# 1. Background

## 1.1 Current status of treatment of atrial fibrillation

Atrial fibrillation (AF) is one of the most common arrhythmias in clinical practice. As of 2010, the number of patients with AF is estimated to be about 33.5 million worldwide, and the number is increasing year by year. An epidemiologic survey covering nearly 30,000 people in 13 provinces and municipalities directly under the central government of China showed that the age-adjusted prevalence of AF was 0.65% and increased with age. The main risks of AF include stroke and thromboembolism, heart failure, myocardial infarction, congestive heart failure, and dementia. The risk of ischemic stroke in patients with AF is four to five times higher than in patients without AF, resulting in a mortality rate of nearly 20% and a disability rate of nearly 60%. Therefore, AF has become one of the major diseases jeopardizing the health of our people.

Percutaneous radiofrequency catheter ablation (RFCA) has become an effective treatment for AF, which can significantly improve the clinical symptoms and cardiac function of patients with AF. However, given the complex pathogenesis and the progressive pathophysiological process of AF, even if the one-year success rate of ablation is satisfactory, there is still a certain recurrence rate in long-term follow-up, and patients still face a certain risk of stroke. Therefore, the latest version of AF management guidelines still suggests that patients with AF after RFCA should choose anticoagulation strategies according to their stroke risks. On the other hand, for patients with AF who need long-term anticoagulation treatment, whether they use warfarin or new oral anticoagulants (such as rivaroxaban, dabigatran, etc.), they have to face the risk of bleeding from long-term anticoagulation and decline in compliance. The above risks can be avoided by percutaneous left atrial appendage occlusion (LAAO). Study shows that LAAO devices represented by the Watchman occluder (Boston Scientific, St. Paul, MN) can significantly reduce the risk of stroke/embolism/bleeding and mortality in patients with AF compared with anticoagulants such as warfarin. LAAO has become an effective treatment for stroke prevention in patients with AF who are contraindicated to anticoagulation or cannot tolerate long-term anticoagulation.

## 1.2 The current status of combined treatment for AF

Based on the above, in 2012, some scholars first tried to combine RFCA and LAAO for AF patients in the same operation, that is, combined treatment for AF. Subsequently, many centers around the world have accumulated experience in the combined treatment of AF. The combined treatment of AF has obvious advantages over the traditional staged procedures: anticoagulants can be stopped after the blanking period of ablation to reduce the risk of long-term anticoagulant relevant bleeding; It can reduce symptomatic events of AF compared with the occlusion-only procedure, and it can also reduce

stroke/embolism events compared with ablation-only surgery; It is safe and reliable, and does not increase the risk of surgical complications; Although the cost of a single operation is high, the total cost is lower than the sum of staged operations, and the cost of long-term treatment is lower; Reduce the number of operations, significantly improve the quality of life and compliance of patients.

Swaans and colleagues first published the single-center combined treatment experience of AF in the world In this study, 30 patients with AF with high risk of stroke or contraindication of anticoagulation were enrolled. They received the implantation of a Watchman occluder and RFCA in a single operation. After one year of follow-up, the maintenance rate of sinus rhythm without antiarrhythmic drugs (AAD) was 70%, and no thromboembolic event was found, which confirmed the feasibility and safety of the combined treatment of atrial fibrillation. Romanov et al. confirmed through a randomized controlled study that LAAO does not affect the success rate of RFCA for AF, thus providing further evidence-based medical evidence for the safety of combined treatment for AF Calvo et al. summarized the experience of combined treatment of AF with different types of left atrial appendage (LAA) occluders. The success rate of postoperative AF-free was 78%, and 97% of patients could safely stop anticoagulant drugs Phillips and colleagues first published the 5-year long-term follow-up results of combined treatment for AF, fully proving the long-term effectiveness and safety of this treatment. Our center was the first to publish a Chinese single-center study of combined treatment for non-valvular AF in China; then we published the first multicenter clinical study of combined treatment for AF in China, jointly with five centers within China. The results of these national and international studies have confirmed the effectiveness and safety of combined treatment for AF. These studies have confirmed the efficacy and safety of combined treatment for AF.

Di Biase et al found that the LAA can be electrically isolated during RFCA of AF, which can improve the success rate of ablation in patients with long-term persistent atrial fibrillation. However, after electrical isolation, the risk of thrombosis and stroke after surgery is also significantly increased due to mechanical contraction function impairment of LAA The combination of LAAO after electrical isolation of LAA caused by ablation can solve this problem, which can not only further improve the success rate of AF ablation, but also avoid the risk of thrombosis and long-term anticoagulation bleeding in such patients. Therefore, combined treatment of AF also expands the ablation strategy of persistent AF, and significantly improves the prognosis of patients with this type of AF.

### **1.3 The impact of different combining strategies on clinical outcomes**

At present, the study on the optimization of combining strategy for combined treatment of AF is very limited, and there is no conclusion on whether the combined treatment with Watchman occluder should adopt the strategy of ablation first or occlusion first.

In the past, many combined studies using the Watchman occluder have used the combining strategy of ablation first followed by occlusion. The combining strategy was not discussed. Walker et al. found that reexamination of transesophageal echocardiography (TEE) 45 days after combined treatment of AF found that some patients had a newly detected peri-device leak (PDL) of no more than 3mm, which may be related to the combining strategy of ablation followed by occlusion. Our retrospective study of 82 combined cases found that when using the Watchman occluder, the proportion of newly detected PDL after the operation with the occlusion-first strategy was significantly lower than that with the ablation-first strategy. If AF ablation is performed first during the operation, the ridge between the left superior pulmonary vein (LSPV) and LAA will produce acute tissue edema. At this time, the LAA sizing and occluder selection are according to conventional standards. Although the occluder can achieve complete occlusion immediately, newly detected PDL may be generated after the tissue swelling subsides, which may even affect the stability of the occluder. However, some scholars found through intraoperative ultrasound tests that there was still a certain distance between the outer edge of the Watchman occluder and the edematous tissue at the ridge after it was expanded, so it was not sufficient to explain the generation of newly detected PDL only by the regression of edema. If the occlusion-first strategy is adopted, there is no interference of tissue edema caused by ablation, and there is no influence on the choice of occluder and compression ratio; however, some scholars are concerned that this will affect the catheter operation of subsequent ablation, and we hold a different viewpoint in this regard.

At present, the efficacy and safety of combined treatment for AF have been widely recognized, but there is no conclusion on the choice of combining strategy, and the limited experience comes from the retrospective analysis of non-randomized studies. Can the occlusion-first strategy reduce the incidence of newly detected PDL after surgery? Will newly detected PDL increase the incidence of device-related thrombus (DRT)? Will it affect the long-term stability of the occluder? Is there any difference in the incidence of long-term thromboembolic events between the two combining strategies? Is there any difference in sinus rhythm maintenance rate between the two strategies after RFCA for AF? These questions need to be answered by further randomized and controlled studies. Therefore, we plan to assess the impact of different combining strategies for the combined treatment of AF with LAAO and RFCA on clinical outcomes through a randomized and controlled study, to provide new and more powerful clinical evidence for more rational guidance of combined treatment of AF.

## 2. Objectives

At present, the strategies of combined AF procedure with Watchman occluder include ablation first and occlusion first, but there is no comparative study on the two. In this study, patients who met the indications of combined treatment for AF were randomly divided into two groups, and they underwent combined procedures with either the occlusion-first or the ablation-first strategy.

### 2.1 Primary objective:

To compare the effects of different combining strategies on the efficacy of combined procedure of LAAO and RFCA.

### 2.2 Secondary objective:

To compare the impact of different combining strategies on the safety and adverse events.

## 3. Study endpoints

### 3.1 Primary endpoints

The primary endpoint was defined as the composite of thromboembolic events such as stroke/transient ischemic attack (TIA), device-related thrombosis (DRT), clinically relevant bleedings, and cardiovascular death or rehospitalization.

### 3.2 Secondary endpoints

3.2.1 Efficacy of radiofrequency ablation: the success rate of AF- and atrial tachyarrhythmia (ATA, including AF, atrial tachycardia [AT], and atrial flutter [AFL])- freedoms at the one-year and long-term follow-up without the antiarrhythmic drugs after the 3-month blanking period.

3.2.2 Efficacy of LAAO: including the incidence of thromboembolic events (including stroke/TIA) and hemorrhagic events during follow-up, and compared with the risk incidence predicted by CHA2DS2-VASC score and HAS-BLED score.

3.2.3 Procedural-related endpoints of LAAO: including the success rate of occlusion, acute complete occlusion rate, operation time, occlusion time (the time from the presence of the occluder to the release of the occluder), X-ray fluoroscopy time, X-ray fluoroscopy dose, etc.

3.2.4 Procedural-related endpoints of AF ablation: including operation time, pulmonary vein isolation time, first-pass isolation (FPI) rate, X-ray fluoroscopy time, X-ray fluoroscopy dose, etc.

3.2.5 Perioperative safety endpoints: Including complications such as acute thromboembolism, pericardial effusion and pericardial tamponade requiring drainage/surgical intervention, device embolization, vascular-related complications, pulmonary vein stenosis, esophageal injuries, phrenic nerve damage, and coronary artery injury.

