#### 8.8.8.2 Postoperative anticoagulation regimen

If there is no contraindication of anticoagulation, anticoagulation treatment should be maintained within 3 months after operation. Those taking warfarin should maintain the target value of INR at 2-3, or take new oral anticoagulants. If no PDL  $\geq$  5mm is found in the TEE visit 45 days after the operation, the anticoagulant treatment can be stopped after the blank period, and the dual antiplatelet therapy (DAPT) can be used instead, that is, clopidogrel 75 mg od + aspirin 100 mg qn, with a course of 3 months. Six months after the operation, it can be changed to single antiplatelet therapy (SAPT), that is, clopidogrel 75 mg od or aspirin 100 mg qn for life.

If PDL  $\geq$  5mm or DRT is found during TEE follow-up after surgery, the duration of oral anticoagulation treatment should be extended regardless of whether the patient has thromboembolic events. It is recommended to recheck TEE after 2-3 months of treatment, and decide the next treatment strategy according to the results. At the same time, adverse events should be recorded (see 8.2 for details).

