## 9. Statistical methods

The random grouping order and statistical analysis of this study were conducted using SPSS software (IBM, USA, version 26.0).

Continuous variables that conform to the normal distribution are expressed as mean  $\pm$  standard deviation, and those that do not conform to the normal distribution are expressed as median (interquartile range IQR). The comparison between groups is performed by t-test or analysis of variance; Classified variables are expressed in terms of rate or composition ratio, and compared between groups  $\chi^2$  Inspection; The results of all time event variables are represented by the median survival time; Kaplan Meier analysis was used to compare the survival rates of the primary endpoint events and the events without atrial fibrillation/ATA between the two groups. COX regression analysis was performed for subgroup analysis of primary endpoint events, and was represented by forest map.  $P < 0.05$  was statistically significant.

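### Section 3.2.2 calls an observed-versus-score comparison the efficacy of LAAO, but every patient also receives ablation and antithrombotic drugs, so a difference from the score cannot be credited to the occluder

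*Protocol*

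**What the plan says.** Protocol section 3.2.2 lists as a secondary endpoint "Efficacy of LAAO: including the incidence of thromboembolic events (including stroke/TIA) and hemorrhagic events during follow-up, and compared with the risk incidence predicted by" CHA2DS2-VASc and HAS-BLED. The label names the occluder as the thing evaluated, and the only comparator named is the score.

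Other sections fix what patients receive and what is counted:

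- **Arms (8.8.1).** Patients are randomised 1:1 to ablation-first or occlusion-first. Both arms are assigned both procedures.
- **Anticoagulation (8.8.8.2).** "If there is no contraindication of anticoagulation, anticoagulation treatment should be maintained within 3 months after operation". With a leak of 5 mm or more, or device-related thrombus, "the duration of oral anticoagulation treatment should be extended regardless of whether the patient has thromboembolic events".
- **Antiplatelets (8.8.8.2).** If the 45-day examination shows no such leak, after the blanking period "the dual antiplatelet therapy (DAPT) can be used instead" for 3 months. From month 6 this can change to lifelong single therapy.
- **Follow-up (5.2.4).** Twelve months, extendable to 2 years or more.
- **Events (8.9.3.8).** Symptomatic and non-symptomatic events are collected: ischaemic stroke, TIA and systemic embolism.
- **Methods (9).** "Classified variables are expressed in terms of rate or composition ratio, and compared between groups"; the methods given there for comparisons are between-group ones.
- **Objectives (2.1, 2.2).** Both concern the effect of different combining strategies.

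**The concern.** Crediting a low event rate to the occluder needs a contrast in which the occluder is what differs. Section 1.2 describes one when it says the combined treatment can reduce "stroke/embolism events compared with ablation-only surgery". This trial has no ablation-only arm, so a published score stands in for the missing control.

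The patients differ from the score's reference population in more than the device. They have been ablated, most are expected to be anticoagulated for roughly the first quarter of a 12-month follow-up, and antiplatelet drugs follow. Section 3.2.2 makes no allowance for any of this. A reduction in thromboembolism from these treatments would be reported as efficacy of LAAO. The bleeding half has the same fault, possibly in the opposite direction, because anticoagulants and dual antiplatelet therapy can raise bleeding.

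At stake is a device-efficacy statement from a trial not designed to support one. Pooling both arms against a score also says nothing about which procedure should come first.

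**Working it through.** **The plan's own figures.** The protocol gives no number for this comparison. Section 7 gives 71 per group and 20% loss: 71 / 0.80 = 88.75, rounded up to 89, as stated. Planned enrolment is 2 × 101 = 202. With 20% loss, 202 × 0.80 = 161.6, about 162.

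**Not in the documents, so assumed.** Predicted thromboembolic rate *r* of 2–6% per year; relative risk 0.36–0.5 on anticoagulation, 0.8–1.0 on antiplatelets, 0.7–1.0 from ablation; occluder effect zero; 12 months of follow-up. Anticoagulation is applied to everyone for 3 of 12 months, which simplifies a conditional rule.

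**Formulas.**
- Predicted events E = N × *r*.
- Multiplier m = (0.25 × RR anticoagulant + 0.75 × RR antiplatelet) × RR ablation × any factor for broader event counting.
- True risk p = *r* × m + any peri-procedural risk.
- Chance of observing fewer than predicted = P(Binomial(N, p) < E).

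**Example.** N = 202, *r* = 4%, so E = 8.08. The exact Poisson 95% upper limit for x events is half the 97.5% chi-square quantile on 2(x + 1) degrees of freedom: 7.22 for x = 2 and 8.77 for x = 3. The upper limit of observed/expected is therefore below 1 only with 2 or fewer events (7.22 / 8.08 = 0.89; 8.77 / 8.08 = 1.09).

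| Inert occluder, plus | m | True mean | P(observed < predicted) | P(2 or fewer) |
|---|---|---|---|---|
| no co-treatment effect | 1.00 | 8.1 | 0.58 | 0.01 |
| anticoagulant 0.36: 0.25 × 0.36 + 0.75 | 0.84 | 6.8 | 0.76 | 0.03 |
| and antiplatelet 0.8: 0.09 + 0.60 | 0.69 | 5.6 | 0.89 | 0.08 |
| and ablation 0.8: 0.69 × 0.8 | 0.55 | 4.5 | 0.96 | 0.18 |
| anticoagulant only, 1% peri-procedural risk added | 0.84 | 8.8 | 0.48 | 0.01 |
| anticoagulant and antiplatelet, events counted 1.5 times more broadly, 1% added | 1.04 | 10.4 | 0.28 | 0.002 |

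**Full assumed range.**
- Co-treatment effects only: 0.72–0.99 at N = 202 and 0.58–0.98 at N = 162.
- No co-treatment effect: 0.56–0.62 and 0.46–0.59.
- With peri-procedural risk of 0.5–1%, with or without events counted 1.3–1.5 times more broadly: 0.20–0.85 over both sizes.

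The observed-to-predicted relation therefore moves in either direction with no occluder effect at all. The bleeding half was not modelled, because the documents give neither predicted bleeding rates nor drug effects on bleeding.

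**The case against.** Much of the case on the other side stands.

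- **No decision rule is stated.** Nowhere does the protocol say that observed below predicted establishes efficacy. A one-sample test or interval may sit in an analysis plan not at hand, so its absence from section 9 is not part of this point. The comparator and the causal label, however, are written into the endpoint itself, and an interval alone would not remove the attribution problem.
- **The score's calibration is not shown.** The protocol does not say which published rates will be used, or whether they describe treated or untreated patients. The direction of bias is therefore not settled.
- **A between-arm look partly exists.** Section 3.2.2 lists event incidence before the score, section 9 compares categorical variables between groups, and the primary composite includes thromboembolic and bleeding events. Still, the only comparator that 3.2.2 names is the score.

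A reader might infer more: that the comparison will favour LAAO more often than not even if the occluder does nothing. The documents do not support this. It needs rates they do not give and a rule they do not state. Chance and discreteness alone put the count below its expectation in 46–62% of trials. Peri-procedural or more broadly counted events can take the figure to 0.20, and bleeding may run against LAAO. Nor do all patients receive 3 months of anticoagulation, since section 8.8.8.2 is conditional. The comparison is not tied to 12 months either: 3.2.2 refers to follow-up generally, and 5.2.4 allows extension.

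**Conclusion.** The point holds as one of attribution. A difference between observed events and the score-predicted rate reflects the occluder, ablation, anticoagulation, antiplatelet drugs, procedural events and event definition together, and this design cannot separate them. That conclusion rests on the protocol's text alone.

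The size of the distortion cannot be derived from the documents, and neither can its net direction. The probabilities above show only how far the result can move under assumed rates. An interval-based rule makes a chance finding much rarer (about 1% in the example with no co-treatment effect). It still yields a favourable result in about 18% of trials with the inert device when all three assumed co-treatment effects act.

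The endpoint is secondary, and neither the primary endpoint nor the randomised comparison of procedure order is affected. The text should be changed, but the defect does not threaten the trial.

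**What to change.** In sections 3.2.2 and 9:

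1. Name the between-arm comparison of thromboembolic and bleeding events as the 3.2.2 analysis.
2. Relabel the score comparison as a descriptive benchmark for the combined regimen, not efficacy of LAAO.
3. State the source of the predicted rates, and count for the benchmark only events of the kind each score predicts. Silent events and TIA should enter only if the predicted rate includes them.
4. For both scores, report observed/expected on full person-time with an exact Poisson 95% interval. Say lower than predicted only if the upper limit is below 1, and even then without crediting LAAO alone.
5. Treat any split by time on and off anticoagulation as supplementary, beside the full result. Anticoagulation is extended for leak or device thrombus, so off-treatment time alone would selectively drop time from the worst-sealed patients and remove the early post-procedural events. Section 8.9.3.3 records drug treatment since the last visit but does not mention stop dates, so these would have to be captured.

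The cost is wording and one small table. A favourable statement about LAAO becomes harder to make: in the 4% example it needs 2 or fewer events against 8.1 predicted. The between-arm contrast will also be imprecise, with about 4 predicted events per arm at that rate (101 × 0.04 = 4.04), so it should be reported with its interval.

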## 4. Enrollment Criteria

All patients with symptomatic AF who met all inclusion criteria and had no exclusion criteria were eligible to participate in the study. All enrolled patients were required to sign a written informed consent. Once enrolled, patients should follow the study protocol's visit schedule and required visits.

### 4.1 Diagnostic criteria

The diagnosis meets the diagnostic criteria for symptomatic AF in the 2016 ESC Guidelines for the Management of Atrial Fibrillation.

### 4.2 Inclusion criteria

4.2.1 Age  $\geq 18$  years;

4.2.2 Symptomatic, nonvalvular atrial fibrillation ;

4.2.3 Refractory to the treatment of antiarrhythmic drugs;

4.2.4 Based on the CHA2DS2-VASc scoring system (stroke risk assessment for patients with nonvalvular atrial fibrillation), a score of  $\geq 2$  ( $\geq 3$  for females) and one of the following :

4.2.4.1 Unsuitable for long-term standardized anticoagulation therapy;

4.2.4.2 Thromboembolic events despite long-term standardized anticoagulation therapy;

4.2.4.3 According to the HAS-BLED scoring system (bleeding risk assessment for patients with nonvalvular atrial fibrillation), scoring  $\geq 3$  points.

4.2.5 Preoperative imaging examinations such as TEE or computed tomography angiography (CTA) assess that the maximum diameter of the ostium at each angle of the LAA is  $\leq 30$ mm, and the estimated effective working depth of the LAA is not less than the maximum diameter of the ostium;

4.2.6 The maximum anteroposterior diameter of the left atrium is  $\leq 55$  mm by transthoracic echocardiography (TTE) before operation;

4.2.7 Subjects or authorized family members voluntarily accept the clinical trial and sign a written informed consent.

